### Outcomes

#### Primary outcomes

The primary outcomes are feasibility and acceptability.

**Feasibility** will be evaluated through: (1) attrition rates: measured by the number of participants who withdrew from the study, (2) EMA response rate: the number and percentage of data collected from EMA surveys relative to the number of potential assessments, as well as the latency between the prompt and participants' response, (3) actigraphy adherence (the threshold is ≥21 hours of wear time per 24 hours across the 14-day protocol).^27^

**Acceptability** will be assessed using a study-specific questionnaire and qualitative interviews. Quantitative indicators will include participant satisfaction, perceived relevance, ease of use and daily burden associated with EMA and actigraphy use.^27 28^ Responses will be rated on a five-point Likert scale (1=strongly disagree to 5=strongly agree). An item will be considered validated if the participant’s score is ≥3/5. Item-level acceptability will be defined as ≥70% agreement for positively worded items and ≤30% agreement for negatively worded items. During the interviews, the interviewer will take notes and, with the participant’s prior consent, audio-record the session. These recordings will be transcribed in a non-verbatim format and analysed using content analysis to identify recurring themes.

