### Sample size

This is a pilot study of feasibility and acceptability, without a quantitative primary outcome measure. As such, a formal sample size calculation is not required. In accordance with recommendations and considering what is reasonable and feasible, we estimate that recruiting 50 participants will provide sufficient variability to assess the feasibility and acceptability of the study.^29 30^ This sample size estimate accounts for an anticipated attrition rate of approximately 20%.

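### The acceptability rule uses one cut-off (≥3 of 5) whatever an item's direction, so midpoint answers favour positively worded items and count against negatively worded ones

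*Protocol article*

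**What the plan says.** The section on primary outcomes opens with "The primary outcomes are feasibility and acceptability". For the quantitative part of acceptability it gives three rules in succession:

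- **Scale.** Five points, with 1 labelled as strong disagreement and 5 as strong agreement. The labels of 2, 3 and 4 are not given.
- **Participant-level cut-off.** "An item will be considered validated if the participant’s score is ≥3/5". No distinction is made between positively and negatively worded items.
- **Item-level thresholds.** "Item-level acceptability will be defined as ≥70% agreement for positively worded items and ≤30% agreement for negatively worded items".

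The article does not say separately which scores make up agreement. The Statistical analysis section adds no definition: its only mention of predefined thresholds concerns participation rates. The end-of-study questionnaire is in a supplementary file that is not part of the text at hand.

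**The concern.** A percentage agreeing needs a score cut-off, and ≥3 is the only one stated. On a symmetric scale anchored at strong disagreement and strong agreement, 3 is equally far from both ends. Counting it as agreement credits a non-committal answer as acceptance on a positively worded item, such as one on ease of use. On a negatively worded item, such as one on burden, the same answer counts as endorsing the complaint.

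The cut-off sentence also ignores direction. A 5 on a burden item meets it and is labelled validated, yet counts against acceptability in the next sentence.

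The Potential implications section says the results will guide item selection, frequency and timing, and the design of a larger study. If wording direction drives the item verdicts, burden could look like a problem and ease of use look settled when participants hold the same attitude to both.

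**Working it through.** **Inputs.** From the Primary outcomes section: the 1–5 scale, the ≥3 cut-off, and the ≥70% and ≤30% thresholds. From the Sample size section: 50 participants with about 20% attrition, so 50 × 0.80 = 40 completers. The plan states no calculated figure for this rule, so there is none to reproduce. All response distributions below are assumptions, because the documents give none.

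**Step 1: the rule in general, reading agreement as ≥3.** Let F be the share with a clearly favourable view, N the share at score 3, and U the share with a clearly unfavourable view, with F + N + U = 100%. On a negative item the raw scores are mirrored (s becomes 6 − s), so U is the share that truly agrees with the complaint.

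- Positive item: agreement = F + N. It passes if F + N ≥ 70%, that is, F ≥ 70% − N.
- Negative item: agreement = U + N. It passes if U + N ≤ 30%, that is, U ≤ 30% − N. Since F = 100% − (U + N), this is the same as F ≥ 70%.

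A negative item therefore always needs 70% favourable, and a positive item needs 70% less the midpoint share. The gap between the two standards is exactly N.

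| N | True agreement needed, positive item | True agreement allowed, negative item |
|---|---|---|
| 0% | ≥70% | ≤30% |
| 10% | ≥60% | ≤20% |
| 20% | ≥50% | ≤10% |
| 30% | ≥40% | 0% |

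**Step 2: the same attitude, worded both ways (agreement as ≥3).**

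| U / N / F | Positive item, F + N | Mirrored negative item, U + N |
|---|---|---|
| 0 / 100 / 0 | 100%, passes | 100%, fails |
| 25 / 40 / 35 | 75%, passes | 65%, fails |
| 15 / 20 / 65 | 85%, passes | 35%, fails |
| 10 / 15 / 75 | 90%, passes | 25%, passes |

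In the last row midpoint answers are few, F already exceeds 70%, and wording makes no difference.

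**Step 3: pass probabilities at the planned size.** With 40 completers the thresholds are 0.70 × 40 = 28 and 0.30 × 40 = 12. Assume F = 50%, N = 25%, U = 25% and use the exact binomial distribution:

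- Positive item: P(X ≥ 28 | p = 0.50 + 0.25 = 0.75) = 0.82.
- Mirrored negative item: P(X ≤ 12 | p = 0.25 + 0.25 = 0.50) = 0.008.

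With all 50 completing (thresholds 35 and 15) the figures are 0.84 and 0.003.

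**Step 4: does moving the cut-off to ≥4 on every item solve it?** Keep ≥70% and ≤30%. If everyone answers 3, the positive item scores 0% and fails, and the negative item scores 0% and passes. For 25/40/35 the positive item scores 35% and fails, and the mirrored negative item scores 25% and passes. In the Step 3 example the two probabilities swap: 0.008 for the positive item and 0.82 for the negative. The asymmetry is reversed, not removed.

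**Step 5: a mirrored rule.** Count raw ≥4 on positive items and raw ≤2 on negative items as favourable, with ≥70% for both. Both wordings then score F: 35% and 35% for 25/40/35 (both fail), 75% and 75% for 10/15/75 (both pass). In the Step 3 example both pass with probability P(X ≥ 28 | 0.50) = 0.008.

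**The case against.** The strongest reply is that the text never equates a validated score with agreement. The ≥3 sentence might be a participant-level label, or might apply after negative items have been recoded. Only the two end points of the scale are labelled, and the questionnaire is not shown. This stands in part: the link is an inference. But if ≥3 is not the agreement cut-off, agreement has no definition in the article and the ≥3 sentence plays no part in the item verdict. Recoding is also hard to square with a ≤30% ceiling, which only makes sense on raw scores.

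A reader might go further and infer that the rule contradicts itself. The documents do not support that. Read as above, the rule gives exactly one result for each item. It is lenient for one wording and strict for the other, which is asymmetry. The direction-free label of validated is awkward, but no two statements exclude each other.

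It is also fair to say that the consequence is limited. The rule describes single items, and the article builds no overall acceptability verdict or go/no-go decision on it. Interviews contribute to the outcome, and the Statistical analysis section also summarises acceptability by means, SDs, ranges and boxplots. A sponsor may further choose to treat absence of disagreement as acceptable, provided it says so and applies the choice alike to both wordings. These points lower the severity but do not remove the asymmetry.

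**Conclusion.** The point holds as a flaw in how a primary-outcome rule is fixed, and it should be corrected before analysis. On the natural reading, a positive item is held to a standard lower than a negative item by exactly the share of midpoint answers: at an assumed 20%, 50% favourable against 70%. Under the assumed 50/25/25 split with 40 completers, the same attitude passes with probability 0.82 in one wording and 0.008 in the other.

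This rests on two assumptions: that ≥3 defines agreement, and that a material share of answers falls on 3. The documents state neither. With few midpoint answers the verdicts can coincide, so the size in this trial is unknown. The number of negatively worded items is also unknown.

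**What to change.** State the rule as follows:

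- Reverse-score negatively worded items (6 minus the raw score).
- Define a favourable response as a recoded score of 4 or 5, that is, raw ≥4 on positive items and raw ≤2 on negative items.
- Call an item acceptable if at least 70% of responses are favourable, for all items.
- Report score 3 as its own category.
- Give the version that counts 3 as favourable (recoded score ≥3) only as a sensitivity analysis.

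Raising the cut-off to ≥4 while keeping the separate 70% and 30% limits is not enough, as Step 4 shows.

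The cost is a short change of wording in the protocol or analysis plan, with no change to data collection. By the algebra in Step 1, verdicts on negative items stay as they are under the ≥3 reading (F ≥ 70% in both), while positive items become harder to pass. Some acceptability figures will therefore be less favourable. Analysis is planned only after inclusion and follow-up are complete, so the rule can be settled before results are examined.

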#### Secondary outcomes

Secondary outcomes will include the examination of immediate and lagged associations between pain, fatigue and sleep and objectively measured physical activity over the 14-day monitoring period, accounting for reciprocal relationships and variations across different times of the day. These analyses will describe both concurrent and delayed effects of these determinants on physical activity. In addition, adherence to and acceptability of two actigraphy devices worn at different body sites will be compared to evaluate their feasibility for assessing physical activity, sleep and sedentary behaviour.

### Sample size

This is a pilot study of feasibility and acceptability, without a quantitative primary outcome measure. As such, a formal sample size calculation is not required. In accordance with recommendations and considering what is reasonable and feasible, we estimate that recruiting 50 participants will provide sufficient variability to assess the feasibility and acceptability of the study.^29 30^ This sample size estimate accounts for an anticipated attrition rate of approximately 20%.

### Eligibility criteria

Adults (≥18 years) with a confirmed diagnosis of RA or SpA, established by a rheumatologist, are eligible for inclusion. Participants must be able to understand and consent to the study protocol, be affiliated with a social security system and have access to a digital device with internet access (eg, smartphone or tablet).

Non-inclusion criteria include: insufficient proficiency in the French language; legal incapacity or deprivation of liberty; major cognitive impairment incompatible with repeated questionnaire completion (eg, Alzheimer’s disease); pregnant or breastfeeding women, as well as individuals with a history of alcohol or substance abuse, or severe psychiatric disorders that could affect adherence to the protocol or the reliability of collected data, are also excluded.

### Recruitment and consent

Physicians and nursing staff in the rheumatology department will inform potential participants about the study and provide them with a flyer, an information sheet and a non-opposition form. Passive recruitment will also be implemented: posters describing the study will be displayed within the rheumatology department. These posters will include a QR code linking to a video created by the research team, which explains the study, how the mobile app works, its objectives and expected outcomes and benefits for patients. The video will be hosted on a dedicated website that also provides additional information about the study. Once the patient’s non-opposition form has been obtained, a research team member will schedule a remote onboarding session to (i) verify eligibility, (ii) assist with app installation and (iii) explain device use. Actigraphy devices will be mailed with a prepaid return envelope.

### Participant timeline and data collection methods

The participant timeline is summarised in figure 1. The study started on 19 November 2025 and will continue until the target sample size of 50 participants is reached, which is expected to occur by the end of March 2026.

**Figure 1 F1:**
[figure not shown]
Study timeline. EMA, ecological momentary assessment.

### Baseline assessment

At study baseline, participants will self-report the following data and questionnaires (for a full list of questionnaires and their description, see online supplemental file 1):

#### Clinical and sociodemographic data

Participants’ clinical characteristics include age, sex, weight, height and body mass index (BMI). Disease-specific variables comprise the type of chronic inflammatory rheumatism (spondyloarthritis or rheumatoid arthritis), disease duration (year of diagnosis), ongoing treatments and self-reported disease activity assessed with a visual analogue scale (VAS).^31^ In addition, sociodemographic information will be collected, encompassing employment status, educational attainment, household composition, living environment and housing type.

#### Questionnaires

Quality of life / physical activity / sleep: Health-related quality of life (EQ-5D-5L),^32^ Global Physical Activity Questionnaire (GPAQ),^33^ Pittsburgh Sleep Quality Index (PSQI),^34^ Inflammatory Arthritis Facilitators and Barriers (IFAB).^35^

Psychological factors: Motivation Scale towards Health-Oriented Physical Activity (EMAPS),^36^ Rosenberg Self-Esteem Scale (RSES),^37^ Pain Catastrophising Scale (PCS)^38^ and Hospital Anxiety and Depression scale (HADS-A).^39^

Fatigue and pain: Pichot Fatigue Scale,^40^ Fibromyalgia Rapid Screening Tool^41^ and pain measured using a VAS.

Disease activity / function (RA & SpA): Bath Ankylosing Spondylitis Disease Activity Index (BASDAI),^42 43^ auto-administered Ankylosing Spondylitis Disease Activity Score with C-Reactive Protein (ASDAS-CRP),^42 44^ auto-administered Disease Activity Score for 28 joints (DAS28)^45^ and the Routine Assessment of Patient Index Data 3 (RAPID3).^46 47^

#### Physical activity and sleep monitors

Participants will be mailed a study kit containing the two actigraphy devices detailed below.

The actigraph GT3X (Actigraph, Pensacola, FL, USA) is a compact device (5.1×4.1 × 1.5 cm) weighing 42 g, designed to record acceleration data as activity counts, providing an objective measure of body movement intensity. Participants will be instructed to wear the actigraph GT3X on their non-dominant wrist continuously for 14 days, except during water-based activities, such as bathing or swimming, during which the device must be removed.

The SENS device (SENS motion, SENS, Copenhagen, Denmark) is a lightweight actigraphy device weighing 20 g, worn on the front of the right thigh and secured with a hypoallergenic adhesive. Similar to the actigraph GT3X, it is worn continuously; however, it does not need to be removed during water-based activities.

#### EMA assessments

EMA details and results will be reported in alignment with an adapted STROBE checklist for reporting EMA studies.^48^ Participants will use the Avicenna app (https://avicennaresearch.com/), which is a General Data Protection Regulation-compliant research tool. To ensure that the items included in the EMA surveys will be relevant and appropriate for the target population, we conducted a simplified content validity procedure. First, items were selected based on a review of the literature on symptom assessment in RA and SpA and on existing validated questionnaires (eg, for pain, fatigue, mood and sleep). Draft items were then reviewed by a multidisciplinary research team (including experts in rheumatology, physical activity and sleep) as well as a patient representative to assess clarity, relevance and feasibility for repeated administration in daily life. Minor adjustments were made accordingly.

Pain related to the disease will be assessed using the following item: *“Please select the number that best corresponds to the intensity of the pain you are experiencing right now”* (Numeric Rating Scale (NRS): 0=no pain, 10=extreme pain). Notifications will be delivered in the morning, at 11:00, 15:00 and 20:30.Fatigue will be assessed using the following item: *“Please select the number that best corresponds to your level of fatigue today”* (NRS: 0=no fatigue, 10=extreme fatigue). Notifications will be delivered in the morning, at 11:00, 15:00 and 20:30.Positive and negative affect will be assessed using items derived from the Circumplex Model of Affect.^49^ The two items *“How happy do you feel right now?”* (NRS: 0=not at all, 10=extremely happy) and *“How relaxed do you feel right now?”* (NRS: 0=not at all, 10=extremely relaxed) will be averaged to obtain a single score of positive affect. The two items *“How worried do you feel right now?”* (NRS: 0=not at all, 10=extremely worried) and *“How depressed do you feel right now?”* (NRS: 0=not at all, 10=extremely depressed) will be averaged to obtain a single score of negative affect. Notifications will be delivered in the morning, at 11:00, 15:00 and 20:30.Sleep quality will be assessed using the following item: *“How would you rate the quality of your sleep last night?”* (NRS: 0=poor, 10=excellent). This notification will be delivered only in the morning.

A full summary of the EMA questions is provided in text Box 1 and the study overview is presented in figure 2.

Box 1EMA surveys within the Avicenna app***Morning only***: How would you rate the quality of your sleep last night?Poor — Excellent (0–10 slider).Please select the score that best reflects the intensity of the pain you are feeling right now.No pain — Extreme pain (0–10 slider).Please select the score that best reflects your level of fatigue right now.No fatigue — Extreme fatigue (0–10 slider).How happy do you feel right now?Not at all happy — Extremely happy (0–10 slider).How relaxed do you feel right now?Not at all relaxed — Extremely relaxed (0–10 slider).How worried do you feel right now?Not at all worried — Extremely worried (0–10 slider).How depressed do you feel right now?Not at all depressed — Extremely depressed (0–10 slider).

**Figure 2 F2:**
[figure not shown]
Study overview.

The application will be installed on participants’ smartphones after being downloaded from the App Store or Play Store. It will be used to send four short questionnaires per day to assess fatigue, sleep quality, positive and negative affect and pain, using a 0–10 scale. The Avicenna app will send audible alerts to participants’ smartphones at predefined intervals.

#### End of study assessments

Participants will complete the end-of-study questionnaire (online supplemental file 2) and participate in an end-of- study qualitative interview after the 14-day EMA collection period (online supplemental file 3).

Any adverse events relating to the use of technology or participating in the study will be recorded. Any serious adverse events will be reported to the sponsor.

### Statistical analysis

Analyses will be conducted once patient inclusion and follow-up are complete. Descriptive statistics will be reported as absolute frequencies and percentages for categorical variables, and as medians with IQRs for continuous variables. Where appropriate, means, SD and ranges (minimum and maximum) will also be provided. A flow diagram will summarise patient recruitment, exclusions and losses to follow-up, including reasons, and will define the final analysis population.

Feasibility and acceptability outcomes will be summarised for the overall study population using means, SD and range values (minimum and maximum). Boxplots will be used to visually depict data distributions. To assess participation rates, data will be dichotomised according to predefined thresholds, allowing estimation of the proportion of patients who declined participation. Reasons for lost to follow-up will be qualitatively analysed. Temporal trends will be described using time series, and response rates will be analysed over time intervals to highlight periods of high and low engagement.

For actigraphy, adherence to the 24-hour wear protocol over 14 days will be evaluated for both devices. Concordance between devices will be examined, and exploratory paired mean comparisons will be used to assess differences in wear time and perceived acceptability. Agreement between categorical acceptability ratings will be evaluated using Cohen’s Kappa coefficient.

### Patient and public involvement

A Patient Research Partner (PRP) living with RA was involved throughout the development of the study. This PRP contributed to refining study documents (protocol and patient information sheet) to ensure clarity and relevance for the target population and helped identify population-specific issues. In addition, the PRP participated in the simplified content validity process by reviewing and providing feedback on EMA items with respect to comprehensibility, relevance and response burden. Finally, the PRP also completed one full testing session of the EMA protocol to evaluate the feasibility of the procedures and identify potential practical issues.

### Potential implications

This study will evaluate the feasibility and acceptability of combining EMA and actigraphy to capture real-time interactions between fatigue, pain, mood, sleep and physical activity in patients with RA and SpA. Findings will guide optimisation of EMA protocols (eg, item selection, frequency, timing) and inform the design of a larger-scale study. The intensive nature of EMA may result in variable adherence or attrition; however, identifying these challenges is a core objective of this feasibility study and will directly inform protocol refinement for future trials.

### Ethics and dissemination

This study was approved by the French national ethics committee [Comité de protection des personnes Nord Ouest I] on 24/07/2025. Notification of the Committee’s approval was forwarded to the National Medicines Safety Agency (ANSM) by the sponsor (Grenoble Alpes University Hospital, Delegation for Clinical Research and Innovation).

### Dissemination of findings

Dissemination plans include presentations of the results at national and international conferences and publication in a peer-reviewed journal.

### Study status

Participant recruitment commenced on 19 November 2025.

## Data Availability

Data sharing not applicable as no datasets generated and/or analysed for this study.
